### Procedures

During the first visit, the doctor or nurse will introduce the study to eligible patients. If the patient is interested in the study; the research nurse will approach the patient and explain to him/her details of the study. At this time, the information sheet will be provided and informed consent will be obtained.

Any participant with known allergy to any ingredient of Moogoo Udder Cream® or the aqeuous cream will receive a patch test to determine a potential reaction with either cream. The patch test entails application of a small amount of the Moogoo Udder Cream® and the aqueous cream to two different sites distal to the irradiated area. This is reviewed after 24 hours for any reaction (a 24 hour timeframe was advised by literature and the RBWH Dermatology specialists). If after 24 hours, the patient is found to have a reaction to either cream, they will not be randomised onto the trial.

Patients allocated to Group one will receive Cream 1. Group two will receive Cream 2. Patients will be asked to start topical application of their allocated cream on the area of skin being irradiated at the onset of radiotherapy, twice a day or more as needed depending on the occurrence of RISR and pain, until the skin reaction subsides. The amount of cream dispensed to each patient will be recorded throughout treatment. If moist desquamation occurs, the topical preparation will be discontinued in the area of skin breakdown and dressings will be applied until the wound heals as per standard care. Patients will be asked to still continue with the topical preparation onto irradiated area that has no breakdown. All participants are given written instructions on how to apply the allocated treatment (see Figure 1).

**Figure 1 F1:**
[figure not shown]
Instructions for cream application.

All other skin care advice given to both groups of patients will be the same, as per the local policy of the Royal Brisbane and Women’s Hospital. All patients will be advised to

wear loose, comfortable cotton clothing in the area being treated

use a gentle detergent

not wear an under wire bra if they are treated for breast cancer

avoid temperature extremes and use lukewarm water to wash

not use hot or ice packs

not use a harsh soap or shampoo on irradiated skin

keep irradiated skin dry

air skin 2–3 times a day

not use a blade razor on irradiated skin

not expose irradiated skin to the sun

not rub or scratch irradiated skin; patients may apply cool moist washers if skin feels itchy or hot

pat skin dry with a soft towel after washing or air dry

not use any tapes, band aids, or dressing unless advised by their clinicians.

not use other topical preparations in the treatment area

rinse off immediately in fresh water if swimming in a pool or salt water (if the skin is intact)

### Discontinuation

If discontinuation of study skin care products occurs due to allergy (or another patient reason), substitution of alternative creams is at the treating clinician’s discretion. Application of both study skin products should cease, as un-blinding for an individual may reveal product types for future patients even though the labelling of the products as 1 or 2 is randomised and the products are very similar in appearance. A variety of other skin products are available so it is unnecessary to continue with either of the study products.

Discontinuation of the study creams does not constitute withdrawal from the study and scheduled assessments should continue as described in this protocol.

### Data collection

Table 3 outlines the measures used in this study. At baseline and weekly during treatment, data will be collected when patients are in the radiation oncology department. At completion of radiotherapy, patients will be given the diaries to complete at home at week 1, week 2 and week 3 post-treatment. The research nurse will contact the patient via telephone to remind them to complete the diaries. At week 4 post-treatment, all patients who have completed their treatments will return to the radiation oncology department for a routine medical review. At this time, they will be asked to complete the final questionnaire and have the severity of their skin reaction assessed by the research nurse.

**Table 3 T3:** Table of study measure

**Measures**	**Administered by**	**Baseline (i.e. Day −7 to Day 0 of radiation treatment)**	**Weekly during treatment (i.e. Day 5, 10, 15, 20, 25, 30 of radiation treatment)**	**Week 1, week 2 and week 3 post treatment (i.e. Day 5, 10, 15 post radiation treatment)**	**4 weeks after radiation treatment Review appointment (Face to face)**
Personal factors (see Table 1)	Research nurse	*			
Radiotherapy factors (see Table 1)	Research nurse	*			
CTCAE	Research nurse	*	*		*
Modified Brief Pain Inventory	Patient	*	*	*	*
Itching	Patient	*	*	*	*
Skindex-16	Patient	*	*	*	*

### Data analysis

Patient characteristics between arms will be compared using the chi-square test for discrete variables and the *t*-test for continuous variables. Acute reactions will be evaluated using Kaplan-Meier actuarial plots (time to event) with the log-rank test for significance. Grade reaction plots at the particular time points (weeks) will be plotted and compared with 95 % confidence intervals for both arms. Uni-variate regression models will determine the significance of factors to be included in the multivariate regression model. A generalized linear interactive modelling package (GLIM4) will be used.

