### Research questions

1. Is there any difference in incidence of Grade 2,3 and 4 RISR between patients with breast, lung and head and neck cancers who receive Moogoo Udder Cream® and those who receive aqueous cream at week 5?

2. Do patients with breast, lung and head and neck cancers who receive Moogoo Udder Cream® for their RISR have a different level of quality of life compared to those who receive aqueous cream at week 5?

3. Do patients with breast, lung and head and neck cancers who receive Moogoo Udder Cream® for their RISR have a different level of pain compared to those who receive aqueous cream at week 5?

4. Do patients with breast, lung and head and neck cancers who receive Moogoo Udder Cream® for their RISR have a different level of itching compared to those who receive aqueous cream at week 5?

5. Is there any difference in time to grade 2, 3 and 4 of RISR between patients with breast, lung and head and neck cancers who receive Moogoo Udder Cream® and those who receive aqueous cream?

6. Are there any differences in RISR, pain, itch and quality of life between groups at all other time points assessed (i.e. week 1,2,3,4,6 of radiation treatment, and 4 weeks post treatment completion)?

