### Baseline characteristics

Baseline characteristics are demographic and clinical variables which include personal factors and radiotherapy factors (see Table 2). These variables are expected to be important for explaining the primary and secondary outcomes in this patient group.

**Table 2 T2:** Summary of baseline characteristics and data collection

**Independent variables**	**Data collection**
Personal factors	Age
	Gender
	Ethnicity
	Stage of cancer (Staging, nodal involvement)
	Comorbidity
	Prior chemotherapy/radiotherapy
	Concurrent chemotherapy/biotherapy (e.g. monoclonal anti-bodies)
	Body mass index
	Smoking
	Cup-size (breast and axilla)
Radiotherapy factors	Daily dose (Gy/fraction)
	Planning target volume (cm3)
	Total dose to region of interest
	Site of radiotherapy
	Radiation technique (External beam via Tomotherapy/Linear accelerator)
	Boost (Yes or no)
	Number of boost treatments

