### Sample size

A sample size of at least 81 in each arm would be required to detect a 20 % difference in the skin reactions scores using a 2-sided significant level of 0.05 and a power of 80 %. Assuming that approximately 5 % will be lost to follow-up; an additional 5 in each group will be required so the final sample will require 172 patients (86 per arm). All eligible patients will be approached consecutively. According to the local statistics of RBWH Cancer Care Services [27], 746 patients receive radical radiotherapy for breast cancer, lung cancer and head and neck cancer over a twelve-month period. Thus, the sample size proposed is achievable over a period of seven months.

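### Pain, itch and Skindex-16 are collected at baseline, but the plan neither states nor guarantees that the week-5 comparisons are adjusted for them

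*Protocol article*

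**What the plan says.** All references are to the protocol article.

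- **Research questions.** Questions 2 to 4 concern skin-specific quality of life, pain and itching. Each asks about the level at week 5. For pain, the question is whether patients on the study cream "have a different level of pain compared to those who receive aqueous cream at week 5". Question 6 extends the same outcomes to the other assessment times.
- **Data collection and Table 3.** "At baseline and weekly during treatment, data will be collected when patients are in the radiation oncology department". Table 3 marks the modified Brief Pain Inventory, itching and Skindex-16 at baseline, defined as Day −7 to Day 0, and weekly during treatment.
- **Baseline characteristics and Table 2.** Table 2 is headed as the independent variables and holds personal and radiotherapy factors only. The text says of them: "These variables are expected to be important for explaining the primary and secondary outcomes in this patient group". No baseline pain, itch or Skindex-16 score is listed.
- **Data analysis.** The only rule on covariates is "Uni-variate regression models will determine the significance of factors to be included in the multivariate regression model". It names neither a candidate list nor an outcome. The section describes analyses for acute reactions and grade, but none specific to the three patient-reported outcomes.

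**The concern.** A patient's own baseline score is often among the better predictors of the later score, and here it is already being collected. The article goes further than staying silent on covariates. It sets out one list of explanatory variables for the primary and secondary outcomes, and one rule by which factors enter a model. The baseline scores are not on the list, and the rule depends on the data.

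There are two ways to read the word factors in Data analysis:

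1. If it means the Table 2 variables, the baseline scores are not candidates.
2. If it is wider, a baseline score enters only when it passes a significance test in the trial's own data. Adjustment is then not fixed in advance and could differ between pain, itch and Skindex-16.

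Neither reading guarantees adjustment. Without it, between-patient differences present at entry stay in the error term, and a chance difference between arms at baseline carries through to the week-5 estimate. Pain is the likeliest place for this to matter, because the trial takes both primary-treatment and postoperative patients across three tumour sites. None of the three scores is a stratification factor.

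**Working it through.** **The plan's own figure.** Sample size states "A sample size of at least 81 in each arm would be required to detect a" 20% difference in skin reaction scores, with a "2-sided significant level of 0.05 and a power of 80"%. Allowing 5% loss, 81 / 0.95 = 85.3, rounded up to 86 per arm and 172 in total, which agrees with the article. The 81 cannot be derived from stated inputs, because no base rate or SD is given. An assumed 80% against 60% gives 82 per arm, which is close. This calculation is for skin reactions and does not depend on the present point.

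**Inputs for the check.**
- From the article: 81 per arm, two-sided 0.05, 80% power.
- Not in the article: the SD and target difference for pain, itch and Skindex-16, and the correlation (rho) between the baseline and week-5 scores. The effect below is an illustration, and rho is shown over a range.

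**Step 1: illustrative effect.** The standardised difference with exactly 80% power unadjusted is d = (1.960 + 0.842) × √(2/81) = 2.802 × 0.157 = 0.44 SD.

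**Step 2: effect of adjustment.** Adjusting for the baseline score multiplies the residual variance by 1 − rho². Power becomes Φ(2.802 / √(1 − rho²) − 1.960).

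| rho (assumed) | Variance reduction | Power |
|---|---|---|
| 0 | 0% | 80.0% |
| 0.1 | 1% | 80.4% |
| 0.2 | 4% | 81.6% |
| 0.3 | 9% | 83.6% |
| 0.4 | 16% | 86.4% |
| 0.5 | 25% | 89.9% |
| 0.6 | 36% | 93.8% |
| 0.7 | 49% | 97.5% |

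At rho 0.5, the adjusted analysis with 81 per arm is worth 81 / 0.75 = 108 per arm unadjusted.

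**Step 3: where the gain reaches 5 points.** Power of 85% needs 1 / √(1 − rho²) = (1.960 + 1.036) / 2.802 = 1.069. Then rho² = 1 − 1/1.069² ≈ 0.125, so rho is about 0.35.

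**Step 4: chance imbalance.** The difference between arms in mean baseline score has an SD of √(2/81) = 0.157 SD. The probability that it exceeds 0.2 SD in either direction is 2 × [1 − Φ(0.2 / 0.157)] ≈ 0.20. With equal SDs at the two times and rho 0.5, a 0.2 SD imbalance moves the unadjusted week-5 difference by 0.5 × 0.2 = 0.1 SD.

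**Step 5: would the screen admit the score?** Suppose the baseline scores are eligible. With 162 patients, t = rho × √160 / √(1 − rho²). This is about 4.7 at rho 0.35 and about 2.6 at rho 0.2. A score correlated strongly enough to matter would usually pass a conventional screen.

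**The case against.** A reader might infer that the covariates come only from Table 2, and so that questions 2 to 4 will compare raw week-5 levels. The article does not support that. Data analysis does not name Table 2, and no analysis is given for these outcomes. A baseline-adjusted model also estimates a between-arm difference in week-5 level, so the wording of the questions fits either method. This objection stands in full and limits the claim to what is neither stated nor guaranteed.

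It can also be said that a condensed article may leave covariates for secondary outcomes to a fuller document. That would dispose of pure silence. Here, however, the article prints a list of explanatory variables and an entry rule, and together they leave the most obvious covariate either off the list or subject to a test.

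The remaining objections concern size, and they have force:

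- No correlation is given, and the 0.44 SD effect is back-solved from a sample size set for another outcome.
- Patients with rash, ulceration or open wounds in the field are excluded, and pain is rated at the irradiated area. Baseline itch and Skindex-16, and perhaps pain, may sit near zero, with little to gain.
- Tumour site is already a stratification factor and a Table 2 variable. If site is in the model, the gain depends on the correlation that remains after site, which may be smaller than the figures above assume.
- If baseline scores are eligible for the screen, Step 5 shows that a useful one would usually enter. The serious loss arises only if they are not eligible.
- Randomisation keeps an unadjusted comparison unbiased over repeated trials, so the issue is precision.

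**Conclusion.** The point holds in a limited form. The three scores are collected at baseline, the only list of independent variables leaves them out, and the only stated entry rule is a significance screen. Adjustment for each outcome's own baseline is therefore not assured for questions 2 to 4 or for the same outcomes in question 6.

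The possible loss is in precision on secondary outcomes. In the illustration it is under 2 points of power at a correlation of 0.2 and about 10 points at 0.5, and it passes 5 points only above about 0.35. These figures assume a continuous score, a 0.44 SD effect, 81 patients per arm and a correlation that the article does not supply, so they show what could be gained and do not measure an actual loss. The primary CTCAE outcome is not affected, because the skin exclusions should leave its baseline close to zero for everyone. The change is worth making because it is nearly free.

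**What to change.** In Data analysis, state that each pain, itch and Skindex-16 scale score, for questions 2 to 4 and the same outcomes in question 6, is compared between arms with a linear model (ANCOVA). The model contains treatment arm and that score's own baseline value from Table 3. The baseline term is prespecified and exempt from the univariate screen.

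Use only baseline scores completed before the first application of cream. The restriction is needed because the baseline window runs to Day 0, cream application begins at the onset of radiotherapy, and the article places baseline collection after allocation. Add the baseline scores to Table 2 so that the list and the analysis agree, covering each pain score and each of the three Skindex-16 scales. The CTCAE comparison needs no such term.

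The cost is a sentence or two of analysis text and a few table rows, with no new data, visits or patients. Each model loses one degree of freedom, and the few missing baseline scores need a simple stated rule, such as simple imputation or a missing indicator.

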The development of RISR may begin immediately, with increasing toxicity occurring at 2–3 weeks, with effects accumulating across the course of treatment, and may persist up to 4 weeks after treatment ends [4]. Hypothesised risk factors influencing RISR reported in the literature are both intrinsic or extrinsic [12]. The intrinsic factors are age, general health, ethnic origin, co-existing diseases, UV exposure, hormonal status [12] and genetic factors [13]. The extrinsic factors include the dose, volume, and number of fractions of radiation, radio-sensitizers, concurrent chemotherapy and the site of treatment [12]. Of these hypothesised factors, smoking status [14] and BMI [14,15] are the major influencing factors supported by empirical data. A range of interventions are used for prophylaxis and management of these reactions. These interventions include (i) topical preparations (both steroidal and non-steroidal), (ii) dressings, (iii) systematic treatment such as amifostine, oral hydrolytic enzymes, pentoxifylline and zinc supplement, (iv) alternating modes of radiation delivery. The latest published systematic review including 39 trials before 2008 reported that only topical corticosteroid agents, among other interventions mentioned above, were found to significantly reduce the severity of some RISR, but not the levels of pain and itching [5]. Further, it is not yet clear which corticosteroid is superior to other non-steroidal agents [5]. This systematic review, together with a number of other previous reviews concluded that the uses of these interventions are not yet supported by conclusive evidence and warrant further investigations [4,5,10,16,17]. Current evidence indicates that there is a paucity of conclusive evidence which can inform health professionals on effective skin management of RISR [18,19].

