### Sequence generation

Blocked randomisation will be performed, with a block size of six, by a computer generated random number list prepared by an investigator who has no clinical involvement in the trial. Stratification by irradiated sites (breast, lung or head and neck), BMI categories (underweight <18.50, normal = 18.50-24.99, overweight =25-29.9, obesity > 30) and smoking status (smoking and non-smoking) will be carried out.

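### Covariates enter the model by univariable significance, so the stratification factors (site, BMI, smoking) can drop out and the adjusted estimate rests on a model chosen from the outcome data

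*Protocol article*

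**What the plan says.** **Analysis.** The Data analysis section of the protocol article sets the covariate rule: "Uni-variate regression models will determine the significance of factors to be included in the multivariate regression model". It states no significance level for entry and names no factor that stays in regardless. The time-to-event comparison reads "Acute reactions will be evaluated using Kaplan-Meier actuarial plots (time to event) with the log-rank test for significance", with no mention of strata.

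**Randomisation.** Under Sequence generation, "Blocked randomisation will be performed, with a block size of six". The stratification is described as "Stratification by irradiated sites (breast, lung or head and neck), BMI categories", with four categories given, followed by "smoking status (smoking and non-smoking) will be carried out".

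**Prognosis.** The Background says that "smoking status [14] and BMI [14,15] are the major influencing factors supported by empirical data". It lists treatment site among the hypothesised extrinsic factors. Under Baseline characteristics, all the variables of Table 2, including site, BMI and smoking, are introduced with "These variables are expected to be important for explaining the primary and secondary outcomes in this patient group".

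No other section overrides the selection rule.

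**The concern.** The design and the analysis treat the same three factors differently. The allocation is built on them, and the article says beforehand that two of them matter most. The analysis then lets a significance test in about 162 evaluable patients decide whether they count.

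Two things are at stake:

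- **Pre-specification.** Table 2 holds 17 candidate variables (10 personal, 7 radiotherapy). With selection on the outcome and no threshold, several different models could be justified from the same data, each with its own adjusted treatment effect.
- **Agreement of analysis with design.** Stratified blocks force the arms to be alike on prognostic factors. An analysis that leaves those factors out does not credit that balance. Its standard error is too large for the design, and the test becomes conservative and loses power. The trial was sized at 80% power, so it has little to give away.

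**Working it through.** **1. The plan's own figure.** The Sample size section gives 81 per arm for a 20% difference, two-sided 0.05 and 80% power, but no base rate. Assume 80% against 60% (40% against 20% gives the same), so the mean rate is 0.70:

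n = [1.960·√(2·0.70·0.30) + 0.842·√(0.80·0.20 + 0.60·0.40)]² / 0.20² = 81.2 per arm.

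Power at 81 per arm is 79.9%. With 5% loss, 81/0.95 = 85.3, so 86 per arm and 172 in total, as stated. The strata number 3 × 4 × 2 = 24, or 172/24 ≈ 7 patients each.

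**2. Simulation of the rule.** None of the following inputs except the design is in the article.

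- Design: n = 162 (2 × 81), 24 strata, permuted blocks of six.
- Assumed mix: sites 60% breast, 15% lung, 25% head and neck; BMI 3/35/34/28% from underweight to obese; 20% smokers.
- Assumed outcome: logistic, 80% at reference covariates, treatment log odds ratio ln(4/1.5) = 0.98.
- Assumed prognostic log odds ratios, moderate / strong / very strong: site ±0.5 / ±1.0 / ±1.8 around breast; BMI extremes ±0.4 / ±0.8 / ±1.2; smoking 0.5 / 0.8 / 1.2.
- Assumed entry rule: univariable p < 0.05, applied to the three stratification factors only. In the fitted models, underweight is merged with normal BMI.
- 4,000 runs per scenario.

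| | Moderate | Strong | Very strong |
|---|---|---|---|
| Smoking fails the screen | 83% | 68% | 54% |
| At least one factor fails | 99% | 85% | 60% |
| Power, three factors fixed | 76.5% | 71.3% | 65.8% |
| Power, screened | 75.4% | 70.0% | 65.2% |
| Power, none included | 74.6% | 65.8% | 52.4% |
| Type I error, fixed | 4.8% | 4.8% | 4.7% |
| Type I error, screened | 4.4% | 4.5% | 4.6% |
| Type I error, none included | 4.2% | 3.3% | 2.0% |

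The failure rates are from runs with a true treatment effect. Power should be compared within a column, because its level falls as the assumed prognostic effects grow.

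- Loss from the screen: 76.5 − 75.4 = 1.1, 71.3 − 70.0 = 1.3, 65.8 − 65.2 = 0.6 points.
- Loss from leaving all three out: 76.5 − 74.6 = 1.9, 71.3 − 65.8 = 5.5, 65.8 − 52.4 = 13.4 points.

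The standard errors show why. Under the null with very strong effects and no covariates, the average model-based standard error is 0.396, but the estimate's actual standard deviation is 0.353. For the screened model the two agree closely (0.462 and 0.467). The screen costs little because it drops a factor mostly when that factor carries little information.

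**3. Second set of assumptions.** Take control rates of 33% (breast), 24% (lung) and 68% (head and neck), odds ratios of 1.65 per BMI category and for smoking, and a 20-point effect. Power is 84.9% screened and 85.1% fixed, with null rejection of 5.3% and 5.4%. With a stronger site effect (25/15/85%), power is 89.0% and 89.5%, with null rejection of 5.6% in both. The gap is 0.2 to 0.5 points.

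**4. Log-rank test.** Assume weekly assessment to week 6, a hazard ratio of 0.58, and site/BMI/smoking log-hazard effects rising over three scenarios from 0.7/0.25/0.25 to 2.0/0.6/0.6, with 3,000 runs each. Power without strata and with site strata is 68% and 71%, 60% and 69%, 43% and 64%. Type I error is 4.7% and 5.0%, 2.8% and 4.1%, 1.5% and 3.1%. The direction is the same as in the logistic model, and the size depends heavily on the assumed site effect.

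**The case against.** The strongest reply is that the rule does almost no numerical harm: about a point of power and a type I error close to 5%. That stands. Three stronger readings are tempting, and the documents do not support them:

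- **That the screen itself costs much power or makes false positives more likely.** The large losses come from comparing a test with no covariates against the fixed model, and the screened model is not that test. The error from omitting stratification factors is conservative, so a positive result would not be undermined.
- **That the treatment arm must also pass the screen.** The article uses the word factors for the personal and radiotherapy variables of Tables 2 and 3, and the arm is not among them.
- **That the plan prescribes an unstratified log-rank test.** It is silent on strata, and a fuller document not shown may settle this. What can be said is that the sentence, taken as worded, describes a test without strata.

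It is also fair to say that the article does not call the multivariable model the primary treatment comparison, and that Sequence generation gives no reason for its choice of strata. Only BMI and smoking are called empirically supported.

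None of this removes the core. The selection rule is stated outright, so it is not a detail left for later. It has no threshold, and it conflicts with the article's own statements about which variables matter.

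**Conclusion.** The point holds as a fault of pre-specification with a small numerical cost. Site, BMI and smoking can each leave the model by chance, and in the first simulation at least one did so in 60% to 99% of trials. The adjusted estimate therefore depends on a covariate set chosen from the outcome data. Under the screen the loss is about 0.2 to 1.3 power points, with type I error near 5%. The loss grows to about 2 to 13 points, with type I error down to 2.0%, in a logistic analysis that ignores the three factors. A log-rank test without strata loses power in the same way.

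The failure rates and losses rest on assumed prevalences, prognostic strengths and an assumed 0.05 entry level. The first simulation screened only the three stratification factors, so it says nothing about the further instability from the other 14 variables of Table 2. This should be fixed because the remedy is free; it is not a condition for the trial's validity.

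**What to change.** Replace the screening sentence in the Data analysis section with a rule fixed before unblinding:

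1. Every regression that compares the arms contains treatment arm, irradiated site, BMI and smoking, whatever their significance. Use BMI as a continuous variable, or state in advance which sparse categories are merged; four levels, with possibly few underweight patients, should not be forced in as they stand.
2. Stratify the log-rank test at least by site. With 24 strata of about 7 patients each, full stratification would be thin.
3. For pain, itching and Skindex-16, also include the baseline value, which Table 3 already collects.
4. Any model that screens the other Table 2 variables is labelled exploratory, with its entry threshold stated.

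The cost is wording only: no new data, no change in sample size and no change to patient care.
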